1. CRITERIA FOR STUDY DISCONTINUATION

- Request by the subject to withdraw
- Request of the primary care provider if s/he believes the study is no longer in the best interest of the subject
- If the subject is found to be pregnant or begins breastfeeding during the course of this study
- If the subject has develops fever, need for systemic therapy for acute or serious illness, or hypotension after screening that precludes completion of the main study visits within the allowed timeframes
- If the patient develops a need for antiretroviral therapy, as determined by the Principal Investigator or by the subject’s primary HIV caregiver
- Requirement for prohibited concomitant medication(s)
- Study drug-related toxicity (see section 7.0 Adverse Event Management)
- Clinical reasons believed life threatening by the physician
- Subject, as judged by the investigators, to be at risk of failing to comply with the provisions of the study protocol as to cause harm to self or interfere with the validity of the study results
- At the discretion of the funding agency

1. STATISTICAL CONSIDERATIONS AND DATA MANAGEMENT

9.1 General Considerations

For all analyses, an intention-to-treat (ITT) approach will be used. That is, study results will be analyzed by the treatment groups to which subjects are randomly assigned, regardless of compliance in taking the medication, adherence to the protocol, and completion of the study. This trial will be a double-blind, randomized, placebo-controlled, two parallel group study. Statistical significance will be considered if two-sided p-values are less than 5%. SAS version 9.1 will be used for all statistical analyses. The software PASS was used for sample size calculation.

9.2 Sample Size Justification

The primary endpoint is change in FMD from baseline to week 8. We used our preliminary data for estimating the detectable difference (Δ) and standard deviation for changes in FMD after 8 weeks with PTX. In the 7 subjects who completed the week 8 visit, an absolute mean (SD) improvement of 4.8% (1.34%) in the change in FMD at week 8 was observed. The 95% confidence interval was 3.5−6.0%. The correlation between week 0 FMD and week 8 FMD was 0.88. We used a very conservative approach, that is, the lower 95% confidence limit for a minimum detectable difference and assumed no change in FMD on average for the placebo group. We also used a conservative approach for estimating the standard deviation in the change in FMD. Our pilot study on 17 HIV positive patients not on cART showed a variability of 2.21 in baseline FMD. Assuming a correlation of 0.30 between week 0 and week8 FMD, we estimated the variability to be 2.62 for the change in FMD which is much higher than the variability we observed in the PTX study.

The sample size was determined based on a two-sample, independent, two-tailed t-test with 5% type I error. Samples sizes were adjusted for an estimated 20% dropout rate. A sample size of 10 per group will have at least 80% power to detect a difference in FMD of at least 3.5% assuming a common standard deviation of 2.62. To adjust for a possible 20% dropout rate, we will recruit 13 per group. The Figure below is a power curve demonstrating the ability to detect various magnitudes of treatment difference assuming a common SD of 2.62.

If a subject withdraws prior to study entry, this subject will be replaced. We expect up to 50 potential subjects will need to be screened to meet the target of 26 randomizations. If we find that the drop-out rate for those on study is greater than the anticipated 20%, then we will replace sufficient numbers of subjects so that the dropout rate is no longer greater than 20%.

9.3. Data Analysis

9.3.1 General Data Analysis

Continuous variables will be summarized by treatment groups using descriptive statistics (e.g., mean, standard deviation, minimum and maximum values). Categorical variables will be summarized using frequency counts and percentages. Baseline clinical and demographic data will be compared between two treatment groups to assess the effectiveness of the randomization. Dichotomous and ordinal variables will be examined using chi-square tests or Fisher’s exact test and continuous measures with Student’s t-tests. If some of the continuous variables are non-normal, a logarithmic or other appropriate transformation will be used to approximate a normal distribution in subsequent analyses that assume normality. Exploratory analyses will be performed to compute p-values which will be presented as an aid to evaluate the overall comparability of the treatment groups at baseline.

#### 9.3.2 Primary Endpoint Analysis

#### The primary outcome is the change in FMD at week 8 of post treatment from baseline. An analysis of covariance (ANCOVA) model will be used to compare the effect of intervention on this outcome variable. The model will include an indicator variable for intervention, baseline FMD, and other potential covariates, including CD4 cell count, HIV-1 RNA level (viral load), age, sex, race, and BMI. We will include covariates one at a time while keeping the intervention and baseline FMD. All covariates except baseline FMD will be excluded from the model if they have insignificant association with the change in FMD. If the response variable does not follow a normal distribution, an appropriate transformation will be used to approximate a normal distribution. The assumption of the constant variance will also be tested, and a transformation will be used if this assumption is violated.

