3.0 STUDY DESIGN

3.1 Overview

The objectives for this study will be met by conducting a randomized, placebo-controlled trial to determine the effects of 8 weeks of PTX on FMD in HIV-infected subjects not requiring cART and without any other significant cardiovascular risk factors (see Schedule of Events below). Based on our pilot data, the eight week design will allow sufficient time to determine if PTX truly improves FMD while being short enough to avoid contamination of cART initiation in the event of a decline in CD4 cell count. The dose of 400mg three times per day is the same dose used in our pilot study.

A total of 26 subjects, 13 in each arm, will be randomized (see Sample Size Estimation below). Up to 50 potential subjects will be screened to achieve the target of 26 randomizations. Because our preliminary data suggest that the improvement in FMD with PTX does not depend on baseline FMD, we will not stratify or limit inclusion based on this latter variable.

There are no published data that suggest that remote use of antiretroviral therapy affects FMD in those not receiving cART. Thus, we will allow subjects to enroll if they have not received antiretrovirals for at least six months prior to screening as opposed to mandating that subjects be completely antiretroviral-naïve to be eligible. Such subjects are likely those who were given cART despite having higher CD4 counts and stopped due to side effects. The six month period was chosen to provide sufficient time to allow washout of their previous therapies and return to baseline immune and virologic states. This criterion matches what we used in our pilot experiments, will increase the potential subject pool, and will make the study more generalizable while not affecting the validity of the final results. We will adjust for previous cART use as a baseline variable in the final analyses.

We will also study peripheral blood markers of inflammation (sVCAM-1, IP-10) that were affected by PTX in our preliminary investigations. Other potential confounding variables, such as smoking status, insulin resistance, dyslipidemia, and waist-hip ratio, will also be measured and adjusted for statistically in the final analyses. Plasma, serum, and urine samples will also be frozen and archived at both the central repository as mandated under the RFA supporting this trial and at our site for future studies of interest.

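### The primary ANCOVA keeps or drops six covariates by their significance in the trial's own data, which lifts the nominal 5% type I error to about 6.5% to 8%

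*Combined protocol and SAP*

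**What the plan says.** Section 9.3.2 analyses the week 8 change in FMD by ANCOVA. Treatment and baseline FMD always stay in the model. Six further candidates are listed: age, sex, race, BMI, CD4 count and viral load. The entry rule is "We will include covariates one at a time while keeping the intervention and baseline FMD" and the removal rule is "All covariates except baseline FMD will be excluded from the model if they have insignificant association with the change in FMD". No retention threshold is given, and nothing says how several retained covariates are combined.

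Section 9.1 sets the level for all analyses: "Statistical significance will be considered if two-sided p-values are less than 5" percent. No section corrects for the selection or names a single fixed primary model.

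Section 3.1 adds other adjustments. It says "We will adjust for previous cART use as a baseline variable in the final analyses", and also "Other potential confounding variables, such as smoking status, insulin resistance, dyslipidemia, and waist-hip ratio, will also be measured and adjusted for statistically". None of these five variables is named in 9.3.2.

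On scale, 9.3.2 says "If the response variable does not follow a normal distribution, an appropriate transformation will be used to approximate a normal distribution", with a similar provision if a test of constant variance fails. The transformation is not named.

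**The concern.** A covariate is retained only when it happens to explain variation in this trial's outcome. Retaining it lowers the residual mean square, and the usual t reference distribution then treats that smaller value as if the model had been chosen beforehand. With 20 to 26 subjects, chance associations are common enough for this to matter. The p-value and confidence interval for treatment then do not have their stated properties.

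The stakes are the main result of a trial that section 2.5 presents as confirming the pilot. Section 9.3.3 applies the same method to the secondary endpoints, although it labels those exploratory. The unreconciled covariate lists and the unnamed transformation leave further room for two analysts who follow the protocol to report different primary models.

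**Working it through.** **1. The plan's own sample size (section 9.2).** Inputs: baseline SD 2.21, week 0 to week 8 correlation 0.30, difference 3.5, two-sided 5% t-test, 20% dropout.

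- SD of change = sqrt(2 × 2.21² × (1 − 0.30)) = sqrt(6.838) = 2.615; the plan states 2.62.
- Exact noncentral-t power with SD 2.62: 80.6% at 10 per arm, 75.8% at 9.
- 10 / (1 − 0.20) = 12.5, so 13 per arm.

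The plan's figures reproduce. The sample size is not in question.

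**2. How often the screen keeps a covariate that has no prognostic value.** With six independent candidates and a keep threshold of p<0.05, the chance of at least one is 1 − 0.95⁶ = 1 − 0.735 = 26.5%. Simulation gives 25.6% at 10 per arm and 26.3% at 13.

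**3. Type I error of the treatment test.** Simulation under no treatment effect used 6,000 trials per row, with FMD SD 2.21 and correlation 0.30. Each covariate was added singly to treatment plus baseline FMD, and all those with p<0.05 were kept together. Covariates were independent, with 25% women and 40% black subjects as anticipated in section 10.7. In the prognostic rows, two covariates each have a coefficient of 0.4 × 2.21 = 0.88 points per SD (an assumption).

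| Per arm | Prognostic covariates | Treatment + baseline FMD, fixed | All six covariates fixed in advance | Rule of 9.3.2 |
|---|---|---|---|---|
| 10 | none | 5.0% | 4.5% | 6.8% |
| 10 | two | 5.1% | 5.4% | 8.0% |
| 13 | none | 5.2% | 4.6% | 6.6% |
| 13 | two | 4.7% | 4.7% | 6.8% |

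The Monte Carlo standard error near 7% is sqrt(0.07 × 0.93 / 6000) = 0.33 points, so even 6.6% lies well above 5%. Repeat simulations of the no-prognostic case gave 6.4% to 7.4%. If the entry rule is read as forward stepwise selection, the range is 6.8% to 9.0%.

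The screening models contain treatment, so adding a constant to one arm does not change which covariates are kept. The nominal 95% interval therefore has the same shortfall at any additive treatment effect: coverage of about 100 − 8 = 92% to 100 − 6.5 = 93.5%.

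**4. The scale rule on its own.** In 20,000 trials per scenario, a Shapiro-Wilk or Levene p<0.05 on the residuals triggered a transformation. One transformation named in advance gave 4.8% to 5.0%. Choosing the most favourable of three gave 5.2% to 5.3% with normal errors and 6.5% to 7.0% with skewed errors.

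**5. Power of the fixed model.** Residual SD = 2.21 × sqrt(1 − 0.30²) = 2.108. At 10 per arm, with an average allowance of 17/16 for chance baseline imbalance, SE = 2.108 × sqrt((2/10) × 17/16) = 0.972. The noncentrality is 3.5 / 0.972 = 3.60 on 17 df, which gives 92.4% power. Simulation gives just under 93%. At 13 per arm the formula gives 97.7%.

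**The case against.** Covariate adjustment is sound practice, and the rule selects on association with the outcome, never on the treatment p-value. When no covariate is prognostic, about 74% of trials keep none of the six, and the result is then exactly the fixed model. The excess is 1.5 to 3 points, in a small study of a surrogate endpoint. All of this is fair. It bears on size and intent, but it does not restore the 5% level. The table also shows that adjustment is not the cause: all six covariates fixed in advance hold the level.

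A reader might infer more than the documents support:

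- **That the two covariate lists contradict each other and themselves break the error rate.** The 9.3.2 list is open-ended, and 3.1 speaks of final analyses without naming the primary ANCOVA. The lists are unreconciled. They inflate error only if someone chooses between them after seeing results, which no section permits.
- **That all eleven variables are screened.** Doing so would give roughly 7.4% to 9.3%, but neither section states that rule. Section 3.1 promises adjustment without a significance screen, and forcing in all eleven gave 5.5% at 10 per arm and 5.0% at 13.
- **That the most favourable single-covariate model would be reported (about 9% to 12%).** The plan does not say so.
- **That the scale is picked by p-value, or that a log of a signed change is prescribed.** Only the variance check is described as a test. The logarithm appears in 9.3.1 as one option for continuous variables generally, and 9.3.2 names none.

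**Conclusion.** The concern holds for covariate selection. As written, the primary test has a type I error of about 6.5% to 8% at 10 to 13 per arm, against about 5% for a model fixed in advance. The size rests on a keep threshold of p<0.05 (not stated in 9.3.2, but the natural reading of 9.1), independent covariates, the plan's SD and correlation, and the assumed prognostic strength. It should be quoted as a range.

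The two covariate lists need reconciling, because the text does not settle which model is primary. The unnamed transformation matters less: it inflates error only if chosen after seeing results. It would also take the estimate off the percentage-point scale on which the 3.5-point target is set.

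**What to change.** Before unblinding, amend section 9.3.2 as follows:

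- Delete the significance-based entry and removal of covariates.
- Name one primary model: treatment plus baseline FMD, on change in FMD in percentage points. Any further covariate must be fixed in advance and kept whatever its p-value. That is also valid; the two-term model is simply the leanest choice.
- Put the remaining covariates in one pre-specified sensitivity analysis, using baseline values and a single list agreed between 3.1 and 9.3.2.
- Judge normality and constant variance on the residuals, and name one fallback, for example a re-randomisation test of the same model. A transformation named in advance would also hold the level, but would lose the percentage-point scale.

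Carry the same rule into 9.3.3. The cost is wording, plus a possible small loss of precision if an omitted covariate is strongly prognostic. The power in step 5 leaves room for that.

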9.3.3 Secondary endpoints analyses

The secondary endpoints are the change in FMD at week 4 and the changes in plasma levels of MCP-1, sVCAM-1, IP-10, fasting lipids, HOMA-IR, CD4 cell count, activated CD8 cell proportions, and HIV-1 RNA level at week 8 from baseline. The secondary analyses will be in exploratory nature and will primarily be used for hypothesis generation. All the secondary outcomes will be analyzed by the same statistical methods as for the primary endpoint. To analyze how the changes in secondary outcomes correlate with changes in FMD, Spearman Rank correlation will be used.

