PTX 400mg three times per day, was given to 9 subjects [128]. Two subjects were removed from study at weeks 2 and 5 due to initiation of prohibited concomitant drugs (inhaled steroid for bronchitis and cART for development of Kaposi Sarcoma, respectively) from their primary caregivers. FMD significantly improved after 4 weeks [median absolute increase 1.5%; p=0.04] and improved further at 8 weeks [median absolute increase from baseline 4.4%; p=0.02]. This degree of improvement in FMD has been associated with reduced risk of future cardiovascular events in the general population[21, 22]. Similar to what was observed with salsalate, 8 weeks of PTX resulted in normalization of FMD. Median NTGMD was 16% at entry and did not change over the course of the trial. It should be noted that the magnitude of improvement in FMD was similar regardless of initial FMD. . Looser stools were noticed by most of the subjects, but in none was this considered to be treatment-limiting. There were no drug-related laboratory toxicities.

We also observed in this pilot study a non-significant decline in triglycerides (p=0.09). No other lipid or metabolic parameter changed with PTX. Viral load did not change. Using an in-house HPLC assay, median plasma PTX concentrations were measured at weeks 4 and 8. The median PTX levels at weeks 4 and 8 were 73 ng/mL (270 nM) and 97 ng/mL (340 nM), respectively. There were no correlations between PTX concentrations and FMD response, which may reflect the small sample size of the study or that there is not a dose-response relationship between plasma PTX levels and FMD. We cannot rule out the possibility that intracellular levels of PTX may correlate with FMD response.

We examined the same peripheral blood markers of various potential inflammatory pathways as in the salsalate trial in order to gain insight into the pathways that may be responsible for the improvement in FMD with PTX. Because of the limited power in this pilot trial, we show in Table 1 those markers that we considered to have changed substantially, defined as either a change > 15% or a p-value < 0.05. Data are presented as median (range) due to small sample size.

Table 1. Markers of pathways that were affected by PTX.

| Biomarker* | Mechanistic Pathway | **HIV-infected Subjects Who Completed the 8 week trial of PTX (N=7)** | | |
| --- | --- | --- | --- | --- |
| Baseline  Median, pg/mL | % Change  (median) | P-value |

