10.2.3 Potential Risks

- There are minimal risks to the subjects enrolled in the proposed research. The first is the potential loss of subject confidentiality. The second consists of the risks associated with blood drawing/needle sticks, which include pain, bruising, infection, and phlebitis. The amounts of blood to be drawn at screening and at each main study visit are 15cc (one tablespoon) and 45cc (three tablespoons), respectively. The total amount of blood to be obtained would be approximately 150cc (10 tablespoons) over at least 11 weeks. The primary risks associated with the use of pentoxifylline are gastrointestinal (nausea, vomiting, dyspepsia), flushing, and dizziness. PTX is a Pregnancy Category C drug and is found in breastmilk. There are no known or potential interactions with antiretroviral medications or commonly used therapies in the HIV-infected population. Nevertheless, we will carefully monitor CD4 counts and HIV-1 viral loads to assess for any potential worsening of immunologic/virologic status for those randomized to PTX during these studies and will be evaluated carefully by the DSMB. The primary risks associated with nitroglycerin administration as part of the brachial artery testing are headache and transient hypotension. NTG may also infrequently cause the sensation of flushing of the skin and rash. There may also be moderate pain associated with the inflation of forearm cuff as part of the brachial reactivity testing.
- The principal alternative to these procedures would be not to participate in the research.

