10.3.2.4 Nitroglycerin. Brachial artery reactivity testing will be performed in a controlled setting in the Indiana Clinical Research Center. To protect against the risks of nitroglycerin administration, registered nurses in the ICRC will monitor the subject’s blood pressure throughout brachial reactivity testing. Subjects with inherent resting hypotension will be excluded from the NTG-mediated flow dilation portion of the brachial reactivity testing. If the subject becomes symptomatic (e.g. dizzy, perspiring, weak or nauseated, or if the systolic blood pressure falls below 80mmHg or more then 30mmHg below their baseline systolic blood pressure, the study will be stopped immediately). The patient will be placed in Trendelenberg position and be given fluids through the previously placed IV heplock if the blood pressure does not recover spontaneously. If the patient develops a headache, an analgesic will be recommended.

10.3.2.5 Withholding Antiretroviral Therapies. Subjects will be included if their HIV caregiver has decided that antiretroviral therapy is not required and thus has been free of cART for at least six months time. There is a minimal risk to the subjects by continuing to refrain from use of antiretrovirals during the short course of this trial (maximum 11 weeks from screening to last main visit). To reduce this small risk, subjects must have CD4 cell counts above 350/µL, which is the level that the Department of Health and Human Services HIV Management Guidelines (<http://aidsinfo.nih.gov/contentfiles/AdultandAdolescentGL.pdf>) states that initiation of ART is not required. Per these guidelines, CD4 cell counts need only be routinely monitored every 3-4 months (12-16 weeks) in the untreated, asymptomatic patient. Therefore, the study course for each subject should be completed by the time their CD4 cell count would normally be rechecked in the clinic. However, if the subject develops signs, symptoms, or conditions associated with a reduction in CD4 cell count, the subject will have their CD4 cell count checked immediately. The principal investigator and the primary caregiver will then decide if antiretroviral therapies should be started immediately with permanent discontinuation of this study.

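### HIV worsening is compared statistically only through week-8 CD4 and HIV-1 RNA change, a value missing for subjects who leave for antiretrovirals before about six weeks of drug

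*Combined protocol and SAP*

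**What the plan says.** - **Risk named.** Section 10.2.3 says of PTX: "we will carefully monitor CD4 counts and HIV-1 viral loads to assess for any potential worsening of immunologic/virologic status". It adds that this "will be evaluated carefully by the DSMB". Safety is a secondary objective in section 1, and the Schema's objectives place safety parameters at weeks 4 and 8.
- **Analysis specified.** Section 9.3.3 lists the secondary endpoints, ending with "HOMA-IR, CD4 cell count, activated CD8 cell proportions, and HIV-1 RNA level at week 8 from baseline". On method: "All the secondary outcomes will be analyzed by the same statistical methods as for the primary endpoint". That means ANCOVA on change (9.3.2). On status: "The secondary analyses will be in exploratory nature and will primarily be used for hypothesis generation".
- **Removal.** Section 8 lists as a reason for study discontinuation: "If the patient develops a need for antiretroviral therapy, as determined by the Principal Investigator or by the subject’s primary HIV caregiver". Under 10.3.2.5, after an unscheduled CD4 check the investigator and caregiver decide whether "antiretroviral therapies should be started immediately with permanent discontinuation of this study".
- **Evaluations on leaving.** Section 6.2.3 provides an early Week 8 evaluation to subjects who give notice after at least 6 weeks of drug, and an early Week 4 evaluation to those who give notice before Week 4 after at least 2 weeks of drug. Those who leave within two weeks after the Week 0 or Week 4 visit get nothing further.
- **Population.** Section 9.1 commits to intention to treat whether or not a subject completes. No missing-data method is given.
- **Data collected.** The Schedule of Events (6.1) has CD4 and HIV-1 RNA at weeks 0, 4 and 8. Section 9.3.3 uses the week-4 values of neither.

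**The concern.** The endpoint needs a week-8 value. The event of most interest, HIV disease worsening enough to call for antiretrovirals, ends participation and often prevents that value from being taken. If PTX did worsen HIV control, its arm would lose more of its worst values than placebo, and the difference in means would shrink toward zero. The intention-to-treat label keeps subjects in their assigned arm but cannot supply a measurement that was never made. Nothing in section 9 counts these subjects by arm. At stake is a possible false statement that PTX has no immunologic or virologic effect. The FMD analysis is not at issue here.

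**Working it through.** **1. The plan's own figure.** The only sample-size figure is for FMD (9.2). SD of change = √(2 × 2.21² × (1 − 0.30)) = 2.61 (stated 2.62). A two-sided two-sample t-test with 10 per group, difference 3.5 and SD 2.62 has power 0.806. Dropout: 10 / 0.80 = 12.5, so 13. It reproduces. No figure is stated for CD4, HIV-1 RNA or antiretroviral starts.

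**2. Who has a week-8 value** (6.2.3 set against section 8):

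| Subject leaves | Evaluation provided | Week-8 CD4/RNA |
|---|---|---|
| Within 2 weeks after Week 0 | None | No |
| After at least 2 weeks of drug, before Week 4 | Early Week 4 | No |
| Within 2 weeks after Week 4 | None | No; Week 4 value exists |
| After at least 6 weeks of drug | Early Week 8 | Yes, if the rule applies |

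The boundary is approximate because the Week 4 visit may be as late as Day 42. The last row is written for subjects who give notice of leaving; whether it covers removal for antiretroviral need is not stated.

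**3. How often.** In the PTX pilot (2.3.3), two of 9 subjects were removed, at weeks 2 and 5 ("inhaled steroid for bronchitis and cART for development of Kaposi Sarcoma, respectively"). So 1 of 9 started antiretrovirals, and a week-5 departure falls in the third row if the Week 4 visit was on schedule. The salsalate pilot had the same CD4 and antiretroviral-free criteria. It lost 3 of 11 subjects, none reported as an antiretroviral start.

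| Rate | Expected in 13 | P(at least one in 13) |
|---|---|---|
| 1/9 = 11% | 13/9 = 1.44 | 1 − (8/9)¹³ = 0.78 |
| 1/20 = 5% | 13/20 = 0.65 | 1 − (19/20)¹³ = 0.49 |

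The exact 95% interval for 1/9 is 0.3% to 48%. At those limits the chance of at least one in 13 runs from about 4% to above 99%.

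**4. Size of the bias, under assumptions.** Let change be normal with SD 1, mean 0 on placebo and −d on PTX. Suppose everyone below −c is removed without a week-8 value and only observed values are analysed. The mean of those who remain is μ + φ(a)/(1 − Φ(a)), with a = −c − μ.

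For d = 0.5 and c = 1.5:
- PTX: −0.5 + 0.242/0.841 = −0.212
- Placebo: 0.130/0.933 = 0.139
- Difference: −0.351, or 70% of the true −0.5

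With c = 1.0 and 2.0 the shares are 56% and 83%. Over d from 0.25 to 1.0 and c from 1.0 to 2.0 the range is 49% to 86%. The documents give no basis for any particular d or c.

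In CD4 units, if 1 to 2 of 13 PTX subjects fell by 150 to 250 cells/µL and left while the others were flat, the full-arm mean would be 1 × (−150)/13 = −12 to 2 × (−250)/13 = −38, against 0 among those remaining. These falls are assumed, and the documents give no CD4 SD to set them against.

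**5. What a count could show.** Fisher's exact test at 13 per arm gives p = 0.22 for 3 versus 0, 0.096 for 4 versus 0 and 0.039 for 5 versus 0. The count would be descriptive.

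**The case against.** The plan does look at this risk elsewhere. The board is to evaluate CD4 and viral load (10.2.3), it receives six-monthly reports of all adverse events (10.6), new diagnoses go on the CRFs (6.3.8.8), and categorical variables are summarized by arm (9.3.1). The endpoints are labelled exploratory. All of this stands, and it limits the point to the specified statistical analysis. None of it sets a statistic or a comparison between arms for antiretroviral need, so it does not repair the reported result.

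Four stronger readings are tempting and are not supported:

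- **The plan would report zero change.** Section 9 never states a complete-case analysis; it is silent on missing values. The zero in step 4 belongs to an assumed example.
- **Every subject who needs antiretrovirals is lost.** Some late leavers may have an early Week 8 evaluation, and many of the others will have Week 4 values.
- **PTX has already been seen to worsen HIV.** The pilot event is one uncontrolled case. No CD4 or RNA fall is reported for that subject, and section 2.5 expects no concern about CD4 decline over eight weeks.
- **Antiretroviral treatment would make harm look like improvement.** Removal is triggered by need, and the leaving evaluation is done as soon as possible after notice. Nothing shows that antiretrovirals would have had time to act. Equally, no rule excludes such values.

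**Conclusion.** The point holds in a limited form. The sole specified statistical comparison for a named risk depends on a measurement that the worsening itself can remove, and the direction of bias is toward no effect. The frequency rests on a single pilot event, giving about 0.65 to 1.4 antiretroviral starts per 13 subjects at the point estimates, with very wide uncertainty. The attenuation to between 49% and 86% of a true effect rests on assumed cut-offs, total loss below them and an observed-values analysis. This is a cheap improvement to an exploratory safety result. It is not a defect in the primary FMD analysis or in the sample size.

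**What to change.** In section 9.3.3:

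1. For all randomized subjects, including any later replaced under 9.2, report by arm the number who, up to discontinuation or last study contact, start or are judged to need antiretrovirals or have a new HIV-related diagnosis. Give an exact confidence interval for the difference and call it descriptive.
2. Analyse change in CD4 and in log10 HIV-1 RNA using every post-baseline value taken before any antiretroviral start (Week 4, Week 8 and early discontinuation evaluations), for example in a repeated-measures model. Exclude values taken after antiretrovirals begin. Sections 9.3.1 and 9.3.2 already allow a log transformation; fix it in advance for RNA.
3. Show the count beside the mean changes.

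Three alternatives are best avoided. Counting to Day 70 needs follow-up that 6.2.3 does not provide for all leavers. A cut-off of 350/µL turns an entry limit into a harm threshold that ordinary variation can cross. Carrying the Week 4 value forward keeps the bias, because it predates later worsening. The repeated-measures model reduces that bias without removing it, which is why the count belongs beside it.

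Cost: analysis wording, one low-precision table and a little more modelling. CD4, RNA, diagnoses and medications are already collected. The documents do not say that the reason for leaving is a CRF item, so one field may be needed. No clinical rule changes.
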